## Methods

### Design

All participants will complete a study visit comprising screening, administration of three reward processing tasks, and completion of a short set of clinical assessments and questionnaires measuring anhedonia/motivational deficits/negative symptoms.

Initially, 8 healthy control participants will be recruited to address any clearly evident implementation issues regarding hardware or software use, and to ensure that mean performance on behavioral tasks and EEG read-outs are broadly in alignment with expectations based on the published literature. Subsequently, individuals with MDD or SZ will be recruited until 37 participants per group have completed the study. Further healthy control participants will be recruited, for a maximum of 80 healthy control participants, to ensure acceptable age and gender matching between healthy control and patient groups.

To investigate test–retest reliability, 16 participants from each group will be recruited to attend a further retest visit 3–5 weeks after the initial visit. The retest visit will comprise re-administration of the task battery as well as a subset of the clinical assessments of anhedonia and negative symptoms. Patients and control groups participating in the retest visit will not be matched, but we will ensure each retest group is broadly representative of its own initial group in terms of age and gender.

The study commenced in September 2019 and is expected to run until the end of Q4 2020, accounting for 3 months of downtime due to the COVID-19 pandemic and resulting Europe-wide lockdowns.

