### Participants and Procedure

Subject recruitment and study visits will take place at four European research centers: Maastricht University, University Hospital Frankfurt, Institute of Neuropsychiatry and Addictions Parc de Salut Mar of Barcelona, and Aristotle University of Thessaloniki. Each center will aim to recruit similar numbers of patients and controls (10 individuals with SZ, 10 individuals with MDD, and 20 healthy controls) and similar numbers of retest participants (4 individuals with SZ, 4 individuals with MDD, and 4 healthy controls). Participants will be 20–55 years of age.

Patients will partly be identified through clinical programs affiliated with the participating research sites, during clinical assessments. Healthy control participants and individuals with MDD or SZ will also be recruited through social media and advertising, and from cohort registers of patients who have agreed to be informed about future studies. Participants will be contacted using their preferred mode of communication. Eligibility of potential participants based on the major study criteria will be assessed via a short telephone screening. Eligible participants will receive the participant information sheet and will be offered adequate time to consider whether or not to participate. Where eligible participants indicate they would like to participate, the study team will help them plan their study visit.

Eligibility criteria are listed in Table 1. At the retest visit, participants will be asked about their recent medical history and medication use to assess their continued eligibility. Baseline data for participants excluded from retest will be included in analyses as long as the eligibility criteria were met at baseline.

**Table 1 T1:** Eligibility criteria.

**Group**	**Inclusion criteria**	**Exclusion criteria**	**Retest visit exclusion criteria**
All participants	Age of 20–55 years	Diagnosis of schizoaffective disorder, bipolar disorder, eating disorder, obsessive-compulsive disorder, post-traumatic stress disorder, attention deficit hyperactivity disorder or autism spectrum disorder (healthy controls and individuals with MDD are also excluded if diagnosed with any psychotic disorder)	Use of opioids, psychostimulants or benzodiazepines within 2 weeks, or diazepam within 4 weeks prior to retest

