### EEG Data Acquisition

To control for variability in EEG recording conditions, an EEG kit, including EEG caps and a specific EEG acquisition system (amplifier and dedicated laptop) will be provided by Biotrial Inc. to each clinical site. At each site, the same EEG kit will be used for the whole set of tests performed during this study. EEG will be recorded on 64 channels, with a sampling frequency of 2,048 Hz and resolution of 16 bits. Raw EEG data will be recorded with a 0.1–70 Hz filter. A digital narrow 50-Hz centered notch filter will be applied to the data to reduce electromagnetic noise due to main power supply. Self-calibration and impedance measurement modules are integrated in the acquisition system.

EEG signals will be collected using EEG caps with electrodes located according to the International 10–20 Jasper system, and conductive gel will be used to ensure good contact between electrodes and the scalp, and to reduce impedance. In order to improve the artifact rejection process, two electrooculography (EOG) channels will be recorded using electrocardiogram patch electrodes. Vertical and horizontal EOG are bipolar channels that detect movements of the eyes and eyelids. Artifacts including high frequency noise due to muscular activity, environmental noise (i.e., electric peak or wire oscillation), and eye or eyelid movements (i.e., blinks) will be rejected by visual inspection.

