Primary and secondary task endpoints will be compared between patient groups and their age and gender-matched controls (two-way group design of MDD and matched controls and also SZ and matched controls). No additional correction for multiple comparisons is planned. Efficacy outcomes for each task will be described by age, gender, site and level of education. These variables will also be adjusted for the case-control comparison, if possible. We will also control for the effects of medication class, given our inclusion criteria permit the participation of medicated patients with SZ and MDD. Prior to database lock and analysis, data on participant medication will be classed according to compound and dose, in consultation with a study psychiatrist. Typical classes for this sample are expected to include atypical antipsychotics, sedatives, SSRIs and other mood stabilizers. A three-way group comparison between the SZ, MDD, and control groups may also be performed.

The study efficacy outcomes will be descriptively summarized by site to explore potential cultural differences that are known to be associated with response. Sites will be considered surrogates to cultural differences since they represent differences in location, language, and potentially in ethnicity.

Further analyses will include anhedonia/motivational scores, as measured by the SHAPS, BNSS, and BIS/BAS, as covariates. This approach will also allow investigation of the influence of anhedonia (and subdomains) on task performance across all participants, regardless of their indication. Furthermore, interactions between clinical assessment scores and group will indicate where effects of anhedonia may be specific to patient group(s).

Test–retest reliability for the three reward processing tasks will be evaluated separately for each participant group using intraclass correlations. Variability of selected task endpoint scores for the same participant across the two time points will be compared with the total variation across all endpoint scores for all participants within each group.

Participants with missing and/or unusable data for any of the three tasks will be excluded from that particular analysis. Where self-report data is missing and/or incomplete, the participant's behavioral data endpoints will still be included in the analysis where possible.

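### The retest ICC sets within-person variation against total variation pooled over four sites, so it can exceed the within-site reliability that a site-stratified or site-adjusted trial would obtain

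*Protocol article*

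**What the plan says.** The Statistical Analyses section of the protocol article states that "reliability for the three reward processing tasks will be evaluated separately for each participant group using intraclass correlations". It then describes the comparison: "Variability of selected task endpoint scores for the same participant across the two time points will be compared with the total variation", where the total covers every score of every participant in the group. Diagnostic group is the only stratifier named.

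Under Design, "16 participants from each group will be recruited to attend a further retest visit 3–5 weeks after the initial visit". Under Participants and Procedure, "Subject recruitment and study visits will take place at four European research centers", and each centre aims for "similar numbers of retest participants (4 individuals with SZ, 4 individuals with MDD, and 4 healthy controls" among its participants.

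On site differences, Statistical Analyses says: "Sites will be considered surrogates to cultural differences since they represent differences in location, language, and potentially in ethnicity". The same paragraph describes cultural differences of this kind as known to be linked with response. Adjustment for site is planned, if possible, for the case-control comparison. Otherwise outcomes are only summarised by site. The Task Selection section lets sites adapt the exact presentation of the tasks to local conventions. For the EEG, "At each site, the same EEG kit will be used for the whole set of tests performed during this study".

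**The concern.** The per-site retest quotas imply that a person's two visits take place at the same centre. A difference between centres that is constant over time is then present in both of that person's scores. It adds to the total variation in the group but not to the variation within the person, so the pooled ICC rises with the between-site variance.

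This matters because the Introduction's objectives call good test–retest reliability a necessary characteristic of a trial endpoint, and the study's purpose is standardised multisite deployment. A later multisite trial that stratifies or adjusts by site removes the site component from its comparison and works with the within-site reliability. A reader who takes the pooled ICC as the figure for such a trial would be somewhat too optimistic. The pooled figure alone does not show how much apparent reliability comes from people and how much from sites.

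**Working it through.** **Inputs from the article.** Four sites with 4 retest participants per group at each give 4 × 4 = 16 per group, which agrees with the Design section. There are two visits per person. The only ICC quoted is 0.63, a published value for the Grip Strength Effort task in the Task Selection section; it serves here as a reference value. The article gives no target, expected value or sample-size reasoning for the retest ICC, so there is no planned figure to reproduce. The 37 per group belongs to the case-control comparison.

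**Assumed input.** The between-site variance is not given. It is varied as a ratio *s* to the within-site total variance.

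**Model.** Score = site + person within site + error, with variances Vs, Vp and Ve. Scale so that Vp + Ve = 1.

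- Within-site ICC: w = Vp / (Vp + Ve).
- Pooled ICC over many sites: (Vs + Vp) / (Vs + Vp + Ve) = (w + s) / (1 + s). This exceeds w whenever s > 0 and w < 1.
- In the actual layout, the sample variance over 16 people drawn 4 from each of 4 sites carries only (16 − 4) / 15 = 0.8 of Vs. The pooled ICC is then approximately (w + 0.8s) / (1 + 0.8s).

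**Results.**

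| s | w = 0.63, many sites | w = 0.63, 4 × 4 layout | w = 0.50, 4 × 4 layout |
|---|---|---|---|
| 0 | 0.63 | 0.63 | 0.50 |
| 0.10 | 0.73/1.10 = 0.66 | 0.71/1.08 = 0.66 | 0.58/1.08 = 0.54 |
| 0.20 | 0.83/1.20 = 0.69 | 0.79/1.16 = 0.68 | 0.66/1.16 = 0.57 |
| 0.30 | 0.93/1.30 = 0.72 | 0.87/1.24 = 0.70 | 0.74/1.24 = 0.60 |

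For w = 0.63 the increase in the 4 × 4 layout is 0.03, 0.05 and 0.07.

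**Simulation check.** In simulated 4 sites × 4 people × 2 visits data with w = 0.63, the median pooled ICC was about 0.66, 0.68 and 0.70 at s = 0.10, 0.20 and 0.30. The ICC with site removed stayed at 0.62 to 0.63 throughout.

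**Read backwards.** Solving the 4 × 4 formula for w at a pooled value of 0.63 gives w = 0.63 − 0.37 × 0.8s. That is 0.60, 0.57 and 0.54 at s = 0.10, 0.20 and 0.30.

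**Precision.** With w = 0.63 and no site variance, the central 95% of simulated pooled ICCs from 16 people runs from 0.22 to 0.85. With site removed it is about 0.17 to 0.86, only slightly wider.

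**The case against.** The strongest reply is that this is a choice of estimand. Within-person against total variation is the ordinary ICC, and for a population mixed over four sites it is correct. That stands: the pooled ICC is not an error, and it is too high only as a statement about within-site reliability. The article does not say how a later trial would be analysed.

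Some site variance may also be genuine person variance. The article treats sites as stand-ins for culture, language and possibly ethnicity, which are stable traits of participants. Removing site removes these too, together with real case-mix differences. This also stands, and it is why the two ICCs belong side by side.

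A reader might infer that separate equipment at each site drives the effect. The article does not support that strongly. One supplier provides the EEG kits, expressly to limit variability in recording conditions, and the system calibrates itself. A constant EEG offset largely cancels in the loss-minus-gain FRN of the Doors task, although a difference in gain would not. The RLWM task has no EEG. No separate grip device per site is documented, and grip targets are calibrated to each participant. Training, manuals, a common script and one platform limit staff effects, although language, culture and permitted local presentation remain.

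A reader might also infer that the ICC always rewards poor standardisation. It does not: site-by-visit shifts or extra visit-to-visit noise would lower it, and the planned summaries by site could expose large offsets.

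A full analysis plan, not shown here, may add a site term. The point rests on the comparator that the article does state.

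**Conclusion.** The point holds in a limited form. As stated, the comparison lets any stable site effect count as between-person variance, and the pooled ICC then exceeds the within-site ICC. The direction follows from the algebra; the size is unknown. It is about 0.03 to 0.07 for an ICC of 0.63 if site variance is 10% to 30% of the within-site total, and zero if there is none. This assumes that both visits take place at the same site and that site effects are constant between visits.

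The shift is small beside the sampling range with 16 people. The article sets no ICC threshold, calls itself a pilot, and has case-control separation as its primary objective, so no decision rule in the article turns on it. The change is still worth making. The authors expect site differences and already plan to adjust for site in the case-control comparison, and the between-site variance is itself evidence on the multisite objective.

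**What to change.** In each diagnostic group, fit the variance-component model with site as a term. Beside the pooled ICC, report the site-adjusted ICC (between-person variance within site, over that variance plus within-person variance) and the between-site variance, all with confidence intervals. Base any statement about reliability for site-stratified or site-adjusted trials on the site-adjusted ICC, and keep the pooled ICC as the description of the mixed four-site population.

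The cost is analysis wording only, with no new data. Three degrees of freedom per group are lost (from 15 to 12 between people), so intervals are slightly wider. With four sites the between-site variance will itself be imprecise. Site adjustment may also remove some genuine case-mix differences, which should be said where the two ICCs are compared.

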### Individual Paradigm Analyses

#### Doors Task

Performance in the Doors task will be analyzed as described previously (61) in terms of modeling the reward feedback stage of the task.

Stimulus-locked ERPs will be averaged separately for losses and gains, using the 200 ms period before stimulus onset as baseline. The primary task endpoint will be the feedback-related negativity (FRN) component of the ERP, defined as the activity on losses minus the activity on gains occurring at the FCz electrode site approximately 300 ms following feedback delivery. The difference score measures neural sensitivity to outcome valence regardless of the source, and this scoring method has been used in a number of prior studies (27, 62–69). Feedback-locked FRN will be averaged separately for each feedback type (i.e., gain, loss) and will be scored as the most negative peak occurring around 300 ms after feedback onset, using a 200 ms period prior to feedback onset as baseline.

The relative effect sizes of other secondary biomarkers, comprising reward positivity (RewP), frontal alpha (8–13 Hz) asymmetry, spectral analysis, and P300 will also be compared. RewP will be quantified as the mean activity in a specified time period after gain feedback onset at FCz. The P300 peak will be defined by its delay following feedback onset, amplitude (μV), latency (msec) and area under the curve (μV^*^msec). Spectral analysis of absolute and/or relative amplitude will be performed in delta, theta, alpha, beta and gamma bands, as defined by the guidelines for the recording and evaluation of pharmaco-EEG data in human participants (70).

#### Grip Strength Effort Task

The primary endpoint for this task will be the percentage of hard grip choices at each reward level (€0.10, €0.20, and €0.40). FRN will be the main reward feedback EEG biomarker of interest, and RewP and frontal asymmetry be investigated in a secondary analysis.

Feedback-locked FRN will be averaged separately for each level of reward value (€0.10, €0.20, and €0.40) and will be scored as the most negative peak occurring 200–400 ms after feedback onset. A 200 ms period prior to feedback onset will be used as baseline. The level of difficulty of the task (easy vs. difficult) will also be considered, to control for cases where the same level of reward (€0.10) could correspond to either a low-effort/low-reward or high-effort/low-reward option. While the Grip Strength Effort task is well-established and has the properties required for generating ERPs at the time of feedback, no electrophysiologically coupled studies that could guide our analyses have been conducted so far. However, based on existing fMRI studies, we assume a certain degree of similarity in electrophysiological responses between the Doors and the Grip Strength Effort tasks.

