**Figure 1 F1:**
[figure not shown]
The Grip Strength Effort task. In the Grip Strength Effort task, participants will complete 4 practice trials, 4 calibration trials, and 54 assessment trials, for a total task duration of approximately 20 min. EEG, electroencephalography; FRN, feedback-related negativity.

During a trial, participants receive visual feedback of the force produced via a thermometer scale marked with a target line, representing the target grip strength. If the participant reaches the target grip strength, they receive the reward associated with their grip strength choice on that particular trial. The task is preceded by a calibration step, which allows for the targets and visual feedback to be tailored to the participant's performance.

Participants complete a series of four practice trials prior to the assessment task. Two of these practice trials present a forced choice to allow the participant to experience both trial types; on the first the participant can only choose the easy task, and on the second they can only choose the hard task. The subsequent two practice trials are identical to the main assessment, in that participants can freely choose either the easy or hard task. The practice trials can be repeated as many times as needed to learn the task, and no performance criterion is required to proceed to the main assessment.

We are not aware of any published studies combining the Grip Strength Effort task with EEG recording, but the straightforward task design readily lends itself to capturing brain activity in the present study.

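### The Grip task FRN is not averaged by target reached or missed, so a difference in hit rate can appear as a difference in FRN

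*Protocol article*

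**What the plan says.** All references are to the protocol article.

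- **Individual Paradigm Analyses, Grip Strength Effort Task.** FRN is named as the main reward feedback EEG biomarker for this task. The averaging rule is: "Feedback-locked FRN will be averaged separately for each level of reward value (€0.10, €0.20, and €0.40"). A second factor follows: "The level of difficulty of the task (easy vs. difficult) will also be considered, to control for cases where the same level of reward". The case meant is the €0.10 level, which a participant may earn through an easy or a hard grip. The score "will be scored as the most negative peak occurring 200–400 ms after feedback onset". No other averaging condition is named and no difference score is defined.
- **The Grip Strength Effort Task (task description, with Figure 1).** Payment depends on performance: "If the participant reaches the target grip strength, they receive the reward associated with their grip strength choice on that particular trial". Targets are individual: "The task is preceded by a calibration step, which allows for the targets and visual feedback to be tailored to the participant's performance". There are 54 assessment trials.
- **Individual Paradigm Analyses, Doors Task.** The parallel sentence uses outcome as the condition: "Feedback-locked FRN will be averaged separately for each feedback type (i.e., gain, loss"). The Doors primary endpoint is a difference, "defined as the activity on losses minus the activity on gains occurring at the FCz electrode site". Doors outcomes are preset at exactly half wins and half losses.

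**The concern.** Grip feedback comes in two kinds: the target was reached and the reward earned, or it was missed and nothing was earned. The averaging rule names reward value and mentions difficulty, but not this distinction. Followed literally, it pools the two kinds of feedback within each reward value, and the weight on each is set by the participant's own success.

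The Doors task is protected twice, because its outcome rate is preset and its averages are split by outcome. The Grip task has neither protection.

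Two comparisons are exposed. In the group comparison, two groups with identical responses to each outcome would get different scores if one missed more often. In the reward-level comparison, the task description gives €0.10 as the example value of the easy grip. On that value, the €0.20 and €0.40 averages come only from hard grips, while the €0.10 average can include easy ones. If misses are more frequent on hard grips, hit rate varies with reward level. The difficulty factor deals with the €0.10 overlap but does not separate outcomes within hard trials.

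At stake is the interpretation of the task's main EEG biomarker. A difference in motor success could be reported as a difference in reward processing, and the scoring could carry into later trials that adopt this task battery.

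**Working it through.** **The plan's own figure.** The only stated figure nearby is the sample size of 37 per group, for percentage of hard choices. For a repeated-measures ANOVA between-group effect with m = 3 measurements, the noncentrality is f² × N × m / (1 + (m − 1)ρ). With f = 0.3516, N = 74 and an assumed ρ = 0.5 (the article gives none), this is 0.1236 × 74 × 3 / 2 = 13.7, and power is 0.955. The figure reproduces, and nothing below depends on it.

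**Effect of pooling outcomes.** Let p be the hit rate, W the mean amplitude after a hit and L the mean amplitude after a miss. The pooled average is

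p × W + (1 − p) × L.

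If patients and controls share the same W and L but have hit rates p₁ and p₀, the patient-minus-control difference is

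(p₀ − p₁) × (L − W),

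that is, the hit-rate gap times the miss-minus-hit amplitude. The article gives neither quantity, so both are assumed over a range:

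| Hit-rate gap | 2 µV | 4 µV | 6 µV |
|---|---|---|---|
| 0 points | 0 | 0 | 0 |
| 5 points | 0.1 | 0.2 | 0.3 |
| 10 points | 0.2 | 0.4 | 0.6 |
| 20 points | 0.4 | 0.8 | 1.2 |

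(Entries in µV.) The sign depends on which group misses more. The product is exact for a mean amplitude. For the planned most-negative-peak score it is approximate, because hit and miss responses may peak at different times.

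**How often would this reach significance?** Take the 0.8 µV cell (20 points, 4 µV), 37 per group, and a two-sided 5% test in the normal approximation.

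- Between-participant SD 2 µV: SE = 2 × √(2/37) = 0.465, and 0.8/0.465 = 1.72. The chance of a significant result in the direction of the artefact is Φ(1.72 − 1.96), about 41%.
- SD 4 µV: SE = 0.930, and 0.8/0.930 = 0.86. The chance is Φ(0.86 − 1.96), about 14%.

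The nominal rate in that one direction is 2.5%. With a 5-point gap and the same 4 µV, the chances are about 6% (SD 2 µV) and 4% (SD 4 µV). The SDs are also assumptions.

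**After splitting by outcome.** Within reached trials the expected mean amplitude is W in both groups, so the hit-rate term disappears whatever the gap.

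**What the split does not remove.** A most-negative-peak score drifts downward as trials become fewer. In a simulation with an assumed true peak of −3 µV and single-trial noise SD of 10 µV, the mean score was −4.7 µV with 18 trials, −5.3 with 12 and −5.9 with 9. Eighteen trials is 54/3, an equal split that is itself an assumption.

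**The case against.** **The article is condensed.** Trial selection for ERP averaging is often left to a fuller document, and Figure 1 is not visible. Nothing says outright that hits and misses will be pooled. This has some force: the full plan may already contain the split. But the article does more than stay silent. It states the averaging conditions for both tasks in parallel sentences, giving outcome for Doors and reward value for Grip. It also says that no earlier EEG study of the Grip task exists to guide the analysis, so no established method fills the gap.

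**The rewarded-trials-only reading.** A reader might infer that the plan fails either way: if only rewarded trials enter, no valence contrast remains and the score is not an FRN. The article does not support this. The Doors section says of its own endpoint that "The difference score measures neural sensitivity to outcome valence regardless of the source", but it also uses the term FRN for a peak scored within one condition, and the Grip section uses that second form. The Grip section never promises a difference score. Comparing groups on reached trials is a sound analysis and is what is recommended below. Only the pooled reading is a problem.

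**Calibration.** Force targets are set as a percentage of each participant's own maximum, which removes much of any difference in baseline strength. This stands as a reason to expect a smaller gap. It does not equalise success over 54 trials, where fatigue and sustained effort can still act.

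**Importance.** The Grip primary endpoint is the percentage of hard choices. The FRN is a non-primary biomarker in a study that describes itself as a pilot. This stands in full.

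**Conclusion.** The point holds in a limited form. As written, the Grip averaging rule leaves out outcome. If all trials at a reward value are averaged, the FRN score depends on hit rate, and a group or reward-level difference in hit rate can pass for a neural one.

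The size cannot be determined from the article. Under assumed amplitudes of 2 to 6 µV and gaps of 5 to 20 points it is 0.1 to 1.2 µV, and it is zero when hit rates are equal. A reader might infer that patients are likely to miss more often than controls. The article reports no hit rates, gives the 90% hard-grip target only as an example, and calibrates to the individual, so it does not support that step. The concern is that the rule would not guard against a gap, not that one is expected.

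The primary objective, the Grip primary endpoint and the sample size are untouched. This is worth correcting because the remedy is a matter of wording and FRN is the task's main EEG biomarker.

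**What to change.** In the Grip Strength Effort Task analysis section:

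1. State that feedback-locked ERPs are averaged separately for target reached and target missed, within reward level and effort.
2. Compare groups and reward levels on target-reached trials.
3. Form a missed-minus-reached difference only for participants with a prespecified minimum number of missed trials.
4. Report hit rate by group, effort and reward level beside the EEG results.

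No new data are needed, since the task already determines the outcome of each trial, and no sample size changes. The cost is fewer trials per average, and some participants will have too few misses for a difference score. Because a peak score becomes more negative as trials become fewer, report the number of trials behind each average. A mean-amplitude score in the same window would avoid that dependence.

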#### The Grip Strength Effort Task

The Grip Strength Effort task (Figure 1) measures participants' willingness to exert effort for variable monetary rewards, a proxy measure for motivation. On each trial, participants choose to perform either an easy or hard grip. The hard grip requires the participant to squeeze a grip force response device at a high percentage of their maximum possible grip strength (e.g., 90%), while the easy grip requires a lesser force (e.g., 50% of their maximum). The easy grip is always worth a specific lower amount (e.g., €0.10), while the reward associated with the hard trial varies (e.g., between three levels of reward value, €0.10, €0.20, or €0.40). The primary dependent variable is the percentage of hard grip choices at the different reward levels.

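### Peak scoring of the Grip FRN makes its size depend on how often the participant chose the hard grip, if averages are formed by chosen value or split by difficulty

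*Protocol article*

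**What the plan says.** The scoring rule is in the Protocol article, Individual Paradigm Analyses, Grip Strength Effort Task. "Feedback-locked FRN will be averaged separately for each level of reward value", with the three amounts €0.10, €0.20 and €0.40, and the component "will be scored as the most negative peak occurring 200–400 ms after feedback onset". The same paragraph adds: "The level of difficulty of the task (easy vs. difficult) will also be considered". The reason given is that "the same level of reward (€0.10) could correspond to either a low-effort/low-reward or high-effort/low-reward option".

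The task description (The Grip Strength Effort Task, under Reward Processing Paradigms) says "On each trial, participants choose to perform either an easy or hard grip" and "The easy grip is always worth a specific lower amount (e.g., €0.10), while the reward associated with the hard trial varies". The legend to Figure 1 states that "participants will complete 4 practice trials, 4 calibration trials, and 54 assessment trials".

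The task's primary endpoint is the percentage of hard choices at each reward level. The FRN is its main EEG biomarker of reward feedback. For the Doors task the article defines a second measure differently: "RewP will be quantified as the mean activity in a specified time period after gain feedback onset at FCz".

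**The concern.** Because the easy grip pays a fixed low amount, every €0.20 or €0.40 outcome follows a hard choice, and every easy choice ends at €0.10. If cells are defined by the value of the chosen option, the number of trials behind each average is decided by the participant. That number follows the percentage of hard choices, which is the quantity on which patients and controls are expected to differ: the Discussion cites earlier work showing less willingness to expend effort in both diagnoses.

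Taking the minimum of a waveform over 200 ms picks out noise as well as signal, and averages of fewer trials are noisier. Two groups with the same brain response but different choices would therefore get different FRN scores. At stake is the reading of the task's main EEG biomarker: a behavioural difference could reappear as a neural one, or a real reduction in FRN at the higher rewards could be masked.

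The Doors task is not exposed in this way. Its 60 trials are fixed at half wins and half losses, so 60 × 0.5 = 30 of each are presented whatever the participant does.

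**Working it through.** **The plan's own figure.** The article gives no figure for the FRN. Its sample size, which concerns the percentage of hard choices, can be reproduced. With f = 0.3516, 3 measurements, 2 groups, N = 74 and an assumed correlation of 0.5 between measurements (not stated), λ = f²·N·m / (1 + (m − 1)ρ) = 0.1236 × 74 × 3 / 2 = 13.7. This gives power 0.955 at 37 per group. That calculation is not in question.

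**Inputs from the article.** 54 assessment trials; three reward values; free choice; minimum over 200–400 ms; 200 ms baseline; 37 per group; α = 0.05.

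**Assumed inputs (not in the article).** Equal split of offers, 54 / 3 = 18 per level; all trials usable; single-trial noise SD 5, 10 or 20 µV; between-person SD 2 or 4 µV; hard choices at the three levels of 10/60/85% in controls and 10/40/60% in patients.

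**Step 1, trial counts by chosen value.**

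| Cell | Controls | Patients |
|---|---|---|
| €0.20 | 18 × 0.60 = 10.8 | 18 × 0.40 = 7.2 |
| €0.40 | 18 × 0.85 = 15.3 | 18 × 0.60 = 10.8 |
| €0.10 | 54 − 10.8 − 15.3 = 27.9 | 54 − 7.2 − 10.8 = 36.0 |

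**Step 2, peak score against trial count.** Simulated 1/f noise, SD 10 µV, true peak −3 µV:

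| Trials | 18 | 14 | 9 | 5 | 3 |
|---|---|---|---|---|---|
| Expected minimum (µV) | −5.39 | −5.83 | −6.77 | −8.46 | −10.44 |

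The mean over the same window stays between −1.32 and −1.34 µV throughout.

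**Step 3, hand check of direction.** With no true component, the expected minimum is proportional to SD/√n. The simulated value at 18 trials and SD 10 µV is −3.69 µV, so the constant is 3.69 × √18 = 15.66. Patients minus controls:
- €0.20: −15.66 × (1/√7.2 − 1/√10.8) = −15.66 × 0.0684 = −1.07 µV
- €0.40: −15.66 × (1/√10.8 − 1/√15.3) = −15.66 × 0.0486 = −0.76 µV
- €0.10: −15.66 × (1/√36 − 1/√27.9) = +0.35 µV

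**Step 4, simulated group comparison.** The true waveform is the same in both groups and between-person SD is 2 µV. Each entry is the false difference in µV with its false-positive rate:

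| Cell | Noise 5 µV | Noise 10 µV | Noise 20 µV |
|---|---|---|---|
| €0.20 | −0.49 (12%) | −1.15 (23%) | −2.47 (31%) |
| €0.40 | −0.32 (8%) | −0.73 (16%) | −1.57 (21%) |
| €0.10 | +0.12 (5%) | +0.29 (8%) | +0.64 (10%) |

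With between-person SD 4 µV the biases are about the same and the rates lower: 8/15/26% at €0.20 and 6/9/17% at €0.40. Averaged over the three cells at SD 2 µV, the shift is −0.23, −0.53 and −1.13 µV.

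**Step 5, what removes it.** Mean amplitude over 200–400 ms gives differences within 0.07 µV of zero and rejection rates of 4–6% in every scenario. The peak score with 18 trials in every cell also holds 4–6%, so the fault lies in combining a peak with counts that depend on choice.

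**Step 6, a minimum trial count.** Further simulations took 70% against 50% hard choices at €0.40 and noise of 8–12 µV, and differed in their remaining assumptions. They gave false-positive rates from 8% to 21% with all cells kept. In those that also dropped cells with fewer than 6 trials, the rates were about 5–8%.

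**The case against.** The strongest objection concerns the meaning of reward level. For the primary endpoint it must mean the offered hard-grip value, since a percentage of hard choices is computed within it. The FRN paragraph uses the same three amounts. If it too means offered value and cells are not split by difficulty, counts are fixed by design and the bias is about zero. This stands as a condition. Against it, the article singles out €0.10 as the amount that could be low or high effort. With offered values every level would mix both grips, so that remark makes sense only for the value of the chosen option. Splitting by difficulty would in any case bring choice back into the counts, although the article says only that difficulty will be considered.

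Second, a minimum trial count removes most of the bias, and an article may leave that rule to a fuller plan. This also stands. Its absence here is not the point; the scoring rule is stated, and it is the rule that creates the dependence.

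Third, RewP is already planned as a secondary Grip analysis, and its only definition, given for Doors, is a window mean. That helps, but leaves the main biomarker as it is.

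Stronger readings are tempting and not supported. A reader might infer that fewer hard choices enlarge the FRN everywhere; at €0.10 the sign reverses. A reader might also compare €0.20 with €0.10 within persons, where false significance reached 61–73% under assumed choice rates of 12/50/75%; the article states no such test. Nor does it state a hypothesis of a blunted Grip FRN: it says that no earlier study combined this task with EEG.

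**Conclusion.** The concern holds, conditionally. If cells are formed by chosen value, the more natural reading, or are split by difficulty, the stated peak score converts differences in choice into differences in FRN. The result is a falsely larger FRN at €0.20 and €0.40 in the group choosing hard less often, a slightly smaller one at €0.10, and hence a spurious group-by-reward pattern.

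The direction in each cell follows from arithmetic; the size does not come from the article. It depends on EEG noise, choice rates, between-person spread and any minimum trial count, all assumed here. The 8–31% range in the two higher cells belongs to between-person SD 2 µV with all cells kept; at 4 µV it is 6–26%. With a minimum of 6 trials it is near nominal at €0.40.

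A reader might infer that the study's main conclusion is at risk. It is not: the Grip FRN is not the task's primary endpoint, and neither the percentage of hard choices nor the 37 per group is touched. The change should nevertheless be made, because the study is meant to prepare these measures for use as trial endpoints.

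**What to change.** Before the EEG data are analysed:
- Score the Grip FRN as mean amplitude at FCz (the site named for Doors) in a window fixed in advance within 200–400 ms, as the article already does in kind for RewP.
- State that cells are formed by the value of the chosen option, and how difficulty enters.
- Keep the most negative peak only as a sensitivity analysis, with trial numbers matched across cells or a minimum count per cell, and report retained trials by cell and group.

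The cost is a few sentences in the analysis plan and no new data. Since the article knows of no earlier Grip study with EEG, comparability with a published Grip FRN is not lost. The one drawback is slightly less sensitivity if FRN latency varies between people.
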